***Outcome and process measures***							
Adult Responses to Children’s Symptoms (ARCS), Protectiveness subscale [51, 52] (primary outcome)	15-item Protectiveness subscale assesses parental protectiveness related to child illness behavior	P/C	X	X	X	X	X
Generalized Anxiety Disorder scale (GAD-2) [53]	2-item measure used for screening of parent anxiety disorder	P/C	X	X	X	X	X
PHQ-2 [54]	2-item measure used for screening of parent depression	P/C	X	X	X	X	X
PROMIS Pain Intensity Scale—Short Form [55]	3-item parent proxy and child self-report assessing child pain intensity in past 7 days	P/C, Ch	X	X	X	X	X
Pain Catastrophizing Scale (PCS)—Short Form [56, 57]	6-item measure that assesses parent catastrophizing thoughts or feelings accompanying the experience of pain	P/C	X	X	X	X	X
Positive and Negative Affect Schedule (PANAS) [58]	One 10-item scale measures parent positive affect and the other 10-item scale measures negative affect on a 5-point Likert scale	P/C	X	X	X	X	X
Multidimensional Scale of Perceived Social Support (MSPSS) [59]	12 items that measure the extent of social support received by parent from 3 sources: friends, family, and significant others. Types of social support assessed by the MSPSS include emotional, tangible, informational, social network support, and esteem	P/C	X	X	X	X	X
Children’s Somatic Symptoms Inventory (CSSI-8) [60]	8 items assess the severity of child’s nonspecific somatic symptoms. The set of GI symptoms (pain, nausea, upset stomach) are used to measure GI symptom severity	Ch	X	X	X	X	X
ROME IV Functional Abdominal Pain Questions [61]	5 items assessing ROME IV criteria for upper and lower child functional abdominal pain—frequency, severity, location, and association with eating (lower only)	P/C	X	X	X	X	X
Pediatric Quality of Life Inventory—Short Form (PedsQL-SF) [62, 63]	Brief measure of child health-related quality of life. The 15 items in the PedsQL comprise four Generic Core Scales: Physical Functioning (5 items), Emotional Functioning (4 items), Social Functioning (3 items), and School Functioning (3 items)	P/C, Ch	X	X	X	X	X
Client Service Receipt Inventory (CSRI) [64]	Validated, comprehensive inventory of health care services incurred due to the child’s symptoms that uses a standard response timeframe of the past 6 months. Parents report on three sources of child health care costs: direct medical service use, direct non-medical costs, and indirect costs	P/C	X		X	X	X

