**Methods:**

Parents with IBS who have children ages 4–7 years are recruited via community-based approaches (e.g., social media advertisements, school electronic distribution, research networks) and health care providers. The target sample is 460 parents randomized to REACH, a web-based social learning and cognitive behavior therapy (SLCBT) intervention or an educational web-based safety comparison condition (EC). Participants will be assessed at baseline, 6-week (immediate post-intervention), 6-month, 12-month, and 18-month follow-up periods (months post-completion of intervention). The primary outcome is change in parental solicitous/protective behaviors. Secondary outcomes include parent risk and protective factors, child health and symptom outcomes, and health care utilization and cost savings.

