##### Social learning and cognitive behavioral therapy (SLCBT) condition

Participants assigned to the SLCBT group will complete a 4-week web-based intervention. The website includes an introductory module, three skills-training modules (i.e., strategies to promote wellness behaviors, use adaptive cognitive coping, model wellness behaviors for their children, and determine when it is appropriate to take further action regarding potential illness in their child), and a brief maintenance and summary module. The web modules were designed to be visually attractive and interactive in order to engage participants through using brief questions to assess participant knowledge, interactive question/answer components, instructional videos, and storyboards that participants can click through. Screenshots can be seen in Fig. 3. Additionally, participants are provided a “Toolbox” in which informational handouts can be accessed, downloaded, and printed. The handouts provide a summary of the knowledge provided in each module. Participants in each group are instructed to log in to the website for 3–4 weeks, approximately 20–30 min per week. Research team members will regularly assess web program usage for all participants and will send reminders up to two times each week as needed to encourage regular usage and completion of all modules.

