***Treatment acceptability, satisfaction, and engagement***							
Treatment Evaluation Inventory—Short Form (TEI-SF) [65]	The TEI-SF is a 4-item measure that assesses treatment acceptability and satisfaction. 9 additional items are intended to collect feedback on the study website	P/C		X			
Treatment engagement (website)	Number of logins to the program, number of modules completed, and number of completed assignments will be measured from the admin backend of the website	N/A		X			

^a^*P/C* Parent/caregiver, *Ch *Child, *N/A *Not applicable

^a^T1*= *baseline, T2 = Post-intervention, 4-6 weeks after baseline; T3 = 6-month follow-up; T4 = 12-month follow-up,  T5 = 18-month follow-up

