Aim 3: Determine cost savings of implementing this preventive intervention on health care expenditures and resource utilization over 18 months. To assess hypothesis 5 (that the SLCBT group will demonstrate cost savings in relation to the EC group), we will first estimate total health care costs in each group, which will be the sum of direct medical costs, direct non-medical costs, and indirect costs. Direct medical costs for each group will be estimated by multiplying utilization estimates for each reported service by the service-specific unit cost from the most recent Medical Expenditure Panel Survey (MEPS) [67], and then summing the costs of all services used. Direct non-medical costs for each arm will be the sum of parent-reported out-of-pocket expenses for special foods, equipment, and transportation to medical appointments. Indirect costs for each arm will be estimated by multiplying parent-reported hours of missed work and leisure time due to caring for their child (i.e., when absent from school due to illness behavior, taking to medical appointments) by the current mean hourly wage for a US worker from the Consumer Price Index of the US Bureau of Labor Statistics [68]. Cost superiority will be indicated by the arm with lower total health care costs if arms are equal in size, or by the average health care cost per family if they are not. Should the SLCBT arm prove superior as hypothesized, intervention-related cost savings per family will be estimated as the difference in average health care costs per family (health care cost/familySLCBT − health care cost/familyEC).

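### If follow-up is timed from completion of the programme, the cost windows miss the 3-6 weeks after randomization, and the baseline cost has no stated role in the comparison

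*Protocol article*

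**What the plan says.** Table 2 (Measures by timepoint) lists the CSRI as the parent-reported source for direct medical service use, direct non-medical costs and indirect costs. It "uses a standard response timeframe of the past 6 months". It is marked at T1, T3, T4 and T5; the T2 cell is blank.

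The Methods paragraph of the abstract dates the later assessments as "6-month, 12-month, and 18-month follow-up periods (months post-completion of intervention". The Table 2 footnote gives "T2 = Post-intervention, 4-6 weeks after baseline" but no starting point for T3-T5, and Outcomes {12} gives none either. Under Intervention description {11a}, "Participants assigned to the SLCBT group will complete a 4-week web-based intervention"; the control programme is also designed for 4 weeks, and both arms are told to log in for 3-4 weeks. Concealment mechanism {16b} places randomization after the baseline measures.

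For Aim 3 (Analyses by aims, {20a}), "we will first estimate total health care costs in each group", with a horizon of 18 months whose start is not given. The arm with the lower total, or the lower average per family if the arms differ in size, is called cost-superior. The saving is the difference in average cost per family. The text does not say which CSRI administrations enter the total, and it mentions no baseline term.

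**The concern.** A randomized cost comparison would normally count everything from randomization. If the first post-baseline window opens only when the programme is finished, any cost incurred during the programme drops out of Aim 3. Those weeks are not neutral in content: one REACH skill is to "determine when it is appropriate to take further action regarding potential illness in their child", so some visits could be prompted or avoided while the programme is running. Main analyses are declared intention-to-treat, and completion is a post-randomization event that is not well defined for families who never finish. An analysis plan cannot repair this, because the data for those weeks are not collected.

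The second matter is efficiency. The CSRI is already collected for the six months before randomization, and earlier care use is likely to predict later care use. The estimator as written does not draw on it.

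**Working it through.** **Inputs**
- Recall window: 6 months before each CSRI (Table 2).
- Administrations: T1, T3, T4, T5 (Table 2).
- Follow-up anchor: completion of the intervention (abstract, the only place an anchor is stated).
- Completion: 3-4 weeks if taken from the log-in instruction and programme length ({11a}); 4-6 weeks if taken as the T2 assessment (Table 2 footnote).
- Horizon: 18 months (Aim 3).
- Assumption: baseline and randomization are treated as the same day.

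**Step 1. Reproduce the stated horizon.** Windows at T3, T4 and T5: 3 × 6 = 18 months, which matches Aim 3. Adding the T1 window would give 24 months, which does not. The 18 months are therefore most naturally the three post-baseline windows.

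**Step 2. Place the windows.** Let g be the time from baseline to completion. The windows are (−6, 0) for T1, then (g, g+6), (g+6, g+12) and (g+12, g+18). The interval (0, g) is in none of them.

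**Step 3. Size of the gap.** One week = 12/52.1775 = 0.230 months. Share of the time from baseline to T5 = g/(18 + g).

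| Completion | g (months) | T5 after baseline (months) | Share uncovered |
|---|---|---|---|
| 3 weeks | 0.69 | 18.69 | 0.69/18.69 = 3.7% |
| 4 weeks | 0.92 | 18.92 | 0.92/18.92 = 4.9% |
| 6 weeks | 1.38 | 19.38 | 1.38/19.38 = 7.1% |

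**Step 4. The other anchor.** If T3-T5 are in fact counted from baseline or randomization, g = 0. The windows are then 0-6, 6-12 and 12-18 months, with no gap.

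**Step 5. Value of the T1 cost.** With a linear baseline covariate correlated r with the outcome, the variance of the arm difference falls by the factor 1 − r². The documents give no r; the range is assumed.
- r = 0.3: reduction 0.3² = 9%; standard error × √0.91 = 0.95.
- r = 0.6: reduction 0.6² = 36%; standard error × √0.64 = 0.80.

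**The case against.** The best defence has four parts.

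First, the anchor appears only in the abstract. If follow-up is run from baseline, nothing is missed. This stands, and it is why the point is conditional. A reader might infer that care during the programme is certainly never counted; the documents support that only if the abstract's timing is the one in use.

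Second, both programmes are nominally 4 weeks, so the gap has the same length in each arm. The conceptual model also puts health care use at the end of the causal chain, so the programme weeks may be where the arms differ least. A reader might infer that the gap favours one arm, but the documents give no basis for a direction. REACH has five modules and the control three, so actual completion times could differ, but nothing shows that they do.

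Third, a post-intervention horizon is a defensible choice, and three 6-month windows fill it exactly. That is fair, but the protocol does not say it has made that choice. Section {11d} promises information on treatments received, yet the CSRI is the only listed instrument covering all three cost components that Aim 3 sums.

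Fourth, covariate adjustment is often left to the analysis plan. A reader might infer that the T1 cost goes unused; the protocol supports only that no use is stated. Nor does omitting it bias the result, since under 1:1 randomization a chance imbalance in high-use families costs precision only. What remains is that the article does name its estimator and decision rule, and neither has a baseline term.

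**Conclusion.** The point holds in a limited form. On the abstract's timing, Aim 3 omits the cost between randomization and completion: nominally 3-6 weeks, or about 4-7% of the time from baseline to T5. The upper end requires completion to be as late as the week-6 assessment. The omission is small and nominally symmetric, its direction is unknown, and it affects the cost aim rather than the primary outcome. It merits action because uncollected weeks cannot be recovered and collection is still under way.

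The lack of a stated role for T1 cost is a loss of precision, not a bias. The 9-36% range rests wholly on the assumed correlation of 0.3-0.6.

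**What to change.** 1. State when the 18-month horizon starts, and give T3-T5 the same anchor in the abstract, Outcomes {12} and Table 2. If follow-up runs from randomization, correcting the abstract is enough to settle the gap.
2. If it runs from completion, add brief CSRI items at T2 covering the time since the baseline survey, for families not yet past T2. This is preferable to lengthening the T3 recall, which would depart from the instrument's standard window. Use the recorded survey dates so that any overlap between the T2 and T3 periods is not counted twice.
3. Report the cost total from randomization. Give the 18-month post-completion total as a sensitivity analysis, because earlier families will lack the T2 items.
4. Estimate the arm difference in mean cost per family with T1 six-month cost as a covariate, and say that T1 cost is not part of the total.

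The cost is a few extra questions at T2 and one covariate that is already collected. Coverage will be incomplete for families already past T2, since recruitment began in October 2023. With recruitment estimated to run to April 2027, families not yet at T2 can still be covered.

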***Treatment acceptability, satisfaction, and engagement***							
Treatment Evaluation Inventory—Short Form (TEI-SF) [65]	The TEI-SF is a 4-item measure that assesses treatment acceptability and satisfaction. 9 additional items are intended to collect feedback on the study website	P/C		X			
Treatment engagement (website)	Number of logins to the program, number of modules completed, and number of completed assignments will be measured from the admin backend of the website	N/A		X			

^a^*P/C* Parent/caregiver, *Ch *Child, *N/A *Not applicable

^a^T1*= *baseline, T2 = Post-intervention, 4-6 weeks after baseline; T3 = 6-month follow-up; T4 = 12-month follow-up,  T5 = 18-month follow-up

#### Plans to promote participant retention and complete follow-up {18b}

Participants will receive automated assessment survey invitations and reminders. Research coordinators will send reminders if assessments are not complete, until the completion of the assessment period. We will use a database checklist to ensure that all study procedures are being followed (including consents) and that all surveys are being completed according to schedule. Study staff will review study participant data and monitor parent responses. Participants will also receive gift card incentives for completing baseline and follow-up assessments. All study questionnaires will be completed online so that participants may complete them at a time and place that is convenient for them.

We will continue to collect outcome data from all participants, irrespective of intervention discontinuation or deviation from protocol. However, we will construct a variable for the amount of treatment completed (number of web-based modules) and conduct sensitivity analyses to evaluate impact on intervention outcomes.

### Data management {19}

All survey data will be collected from parents online through Research Electronic Data Capture (REDCap). Research coordinators will track assessment completion regularly, monitor for any missing data, and follow up with participants when missing data are identified. Research coordinators will also use REDCap alerts, reports, and queries to minimize missing data and ensure accuracy. Additionally, study staff will monitor for data irregularities such as skip patterns and out of range data and completion times. The REDCap database will require online sign-in with a username and password assigned to individual study staff; all data stored in REDCap will be retained on a secure server accessible only to study staff. Scoring of study measures will be done via syntax to minimize errors.

### Confidentiality {27}

The subject’s identity, research records, and personal health information will be safeguarded using secure password-protected servers. The primary source of data will come from questionnaires, which will be stored electronically in REDCap (secure password-protected database). All data will be coded with a unique participant ID. The software will be hosted on a secure, HIPAA-compliant server. Only the research team and the Seattle Children’s IRB will be able to access the participant data and information collected from this study. All research data will be de-identified at the earliest possible opportunity to promote data sharing.

Given this is an online study, it is important that user information and data be protected from theft, alteration, or unauthorized access of any kind. We have developed a User Privacy Policy and a Terms of Use Agreement for the REACH web program as per standard. Use of the web program will indicate agreement and acceptance of the Terms of Use. Only study identification numbers will be used to identify participants on the website. The web program will not collect or ask for information that can be used to identify the participant. Seattle Children’s will not sell or rent information collected by the web program to others.

### Plans for collection, laboratory evaluation, and storage of biological specimens for genetic or molecular analysis in this trial/future use {33}

N/A: As stated in Sect. 26b, no biological specimens will be collected for this study.

## Statistical methods

### Statistical methods for primary and secondary outcomes {20a}

#### General analytic procedures

All main analyses will be intention-to-treat analyses, including all participants randomized regardless of intervention compliance. Missing values due to dropouts will be imputed with well-established methods that reduce bias in estimates such as multiple imputation, full information maximum likelihood, and empirical Bayes estimation, or multiple imputations with chained equations (MICE), if a substantial amount of missing data exists.

#### Analyses by aims

Aim 1: Determine the efficacy of a preventive SLCBT intervention delivered to parents with IBS compared to a time and attention placebo/education condition (EC) at post-intervention, and at 6-, 12-, and 18-month follow-up periods. Analyses for this aim will use an intent-to-treat and dose–response approach. Intent-to-treat analyses will test associations between a dichotomous treatment assignment variable and primary (hypothesis 1) and secondary parent outcomes (hypothesis 2), as well as child health and symptom outcomes (hypothesis 3). Efficacy tests will be conducted using multilevel modeling (MLM) to maximize power and account for the longitudinal design with nesting of observations within person/family. In addition, the use of multilevel modeling allows estimation of intervention effects at a specific time point (intercept) and change over time in intervention effects (slope; time × intervention interaction). For example, to test hypothesis 1, we will estimate a series of MLMs testing the effect of the dichotomous intervention assignment variable on the level (intercept) of Adult Response to Children’s Symptoms (ARCS) scores at each time point by systematically re-centering the intercept (e.g., model 1: intercept at post treatment, model 2: intercept at 6 months, etc.). Next, we will test the association between intervention assignment and the slope of ARCS scores across time points (time × intervention interaction). Controls will include parent age and sex, as well as child sociodemographic characteristics and parent pre-treatment irritable bowel syndrome severity. Dose–response analyses also will use MLM as described above; however, the dichotomous treatment assignment variable will be replaced with a treatment engagement score (e.g., modules completed).

Aim 2: Determine the contribution of changes in parental risk and protective factors as mediating treatment effects. Hypothesis 4 states that changes in parental risk and protective factors will mediate treatment effects on child health-related quality of life. Following the procedures outlined by Muthen and colleagues [66], we will test whether and to what extent parent pain catastrophizing mediates the association between intervention group and parent solicitous responses to child symptoms. Similar models will test other mediators, as well as secondary parent and child outcomes.

Aim 3: Determine cost savings of implementing this preventive intervention on health care expenditures and resource utilization over 18 months. To assess hypothesis 5 (that the SLCBT group will demonstrate cost savings in relation to the EC group), we will first estimate total health care costs in each group, which will be the sum of direct medical costs, direct non-medical costs, and indirect costs. Direct medical costs for each group will be estimated by multiplying utilization estimates for each reported service by the service-specific unit cost from the most recent Medical Expenditure Panel Survey (MEPS) [67], and then summing the costs of all services used. Direct non-medical costs for each arm will be the sum of parent-reported out-of-pocket expenses for special foods, equipment, and transportation to medical appointments. Indirect costs for each arm will be estimated by multiplying parent-reported hours of missed work and leisure time due to caring for their child (i.e., when absent from school due to illness behavior, taking to medical appointments) by the current mean hourly wage for a US worker from the Consumer Price Index of the US Bureau of Labor Statistics [68]. Cost superiority will be indicated by the arm with lower total health care costs if arms are equal in size, or by the average health care cost per family if they are not. Should the SLCBT arm prove superior as hypothesized, intervention-related cost savings per family will be estimated as the difference in average health care costs per family (health care cost/familySLCBT − health care cost/familyEC).

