### Outcomes {12}

The primary outcome is change in parental solicitous/protective behaviors. Secondary outcomes include parent risk and protective factors and child health and symptom outcomes. Participant outcomes will be assessed at baseline, immediate post-intervention (6 weeks) and at 6-month, 12-month, and 18-month follow-up periods. See also Sects. 6a and 18a.

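### Re-centering the intercept of a one-slope model reads every visit's ARCS effect off one line; if time is linear and baseline is a modelled outcome, the post-intervention effect is understated by about 40%

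*Protocol article*

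**What the plan says.** Statistical methods {20a}, Analyses by aims, Aim 1, chooses multilevel models partly because the approach "allows estimation of intervention effects at a specific time point (intercept) and change over time in intervention effects (slope; time × intervention interaction". The arm effect on the level of ARCS is tested "at each time point by systematically re-centering the intercept"; the examples given start at post-treatment and then move to 6 months. The next step is a single trend: "we will test the association between intervention assignment and the slope of ARCS scores across time points (time × intervention interaction". No categorical, quadratic or piecewise time term is mentioned.

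Four other statements bear on how that model behaves:

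- Outcomes {12}: "The primary outcome is change in parental solicitous/protective behaviors".
- Aim 1 covariates: "Controls will include parent age and sex, as well as child sociodemographic characteristics and parent pre-treatment irritable bowel syndrome severity". Baseline ARCS is not among them.
- Table 2 has ARCS measured at all of T1 to T5, and its footnote gives "T2 = Post-intervention, 4-6 weeks after baseline; T3 = 6-month follow-up; T4 = 12-month follow-up", with T5 at 18 months. The Abstract counts the later follow-ups from completion of the intervention.
- Intervention description {11a}: "Participants assigned to the SLCBT group will complete a 4-week web-based intervention". The whole programme therefore falls between T1 and T2.

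**The concern.** Re-centering needs a continuous time variable. With one slope per arm, moving the origin from visit to visit changes the label on the intercept but not the fit: the models in the series are one model written several ways. What is reported as the effect at T2, T3, T4 or T5 is a point on one line, right only if the arm difference really is linear over the modelled period.

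The design makes that doubtful once baseline is included. Randomization follows baseline measurement, so the expected arm difference at T1 is zero. An intervention that works during its 4 weeks produces a jump between T1 and T2, followed by a plateau or a fade. A straight line cannot follow a jump and a plateau.

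Aim 1 asks about efficacy at post-intervention and at 6, 12 and 18 months. A misfitting line can understate the immediate effect, overstate the latest one, and give a slope test that mixes the initial response with later change. The same approach is planned for the secondary outcomes and the dose–response analyses.

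**Working it through.** **Inputs from the protocol.** Visits T1 to T5; effect size 0.30 to 0.40 SD, alpha 0.05 (Sample size {14}); target 460, 1:1, so 230 per arm.

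**Assumptions.** Times 0, 1.5, 7.5, 13.5 and 19.5 months; linear time; SD 1; compound symmetry with correlation ρ of 0.5 to 0.7; complete data; two-sided test. Effects are absolute ARCS differences in SD units.

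**The plan's own figures.** There is none for the re-centered model. An ordinary two-arm calculation gives a total N of 4(1.96 + 0.842)²/d² ≈ 4 × 7.85/0.09 = 349 at d = 0.30, and 4 × 7.85/0.16 = 196 at d = 0.40. The plan states 380 and 210. Its software inputs are not given and its figures are the larger ones, so no error is shown there.

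**Step 1: line with T1 in the outcome vector.** With balanced data and this covariance, generalised least squares gives the same line as ordinary least squares.

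- Mean time = 42/5 = 8.4. Deviations d: −8.4, −6.9, −0.9, 5.1, 11.1. Sum of squares = 268.2.
- Slope = Σ(d × effect)/268.2. Fitted value = mean effect + slope × d.

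*Held effect, 0/0.30/0.30/0.30/0.30.* Mean 0.24; slope = 0.30 × 8.4/268.2 = 0.0094 per month.

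| | T1 | T2 | T3 | T4 | T5 |
|---|---|---|---|---|---|
| True | 0 | 0.30 | 0.30 | 0.30 | 0.30 |
| Line | 0.161 | 0.175 | 0.232 | 0.288 | 0.344 |

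At T2: 0.24 − 6.9 × 0.0094 = 0.175, which is 42% too small. The 12-month error is only −0.012.

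*Fading effect, 0/0.40/0.30/0.20/0.10.* Mean 0.20; slope = −0.90/268.2 = −0.0034.

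| | T1 | T2 | T3 | T4 | T5 |
|---|---|---|---|---|---|
| True | 0 | 0.40 | 0.30 | 0.20 | 0.10 |
| Line | 0.228 | 0.223 | 0.203 | 0.183 | 0.163 |

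A true fall of 0.30 between T2 and T5 is shown as 0.06. The 18-month value is 63% too large; the 12-month error is again small (−0.017).

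**Step 2: power at 230 per arm.** The variance of the fitted arm difference is (2/230) × [ρ + (1 − ρ)(1/5 + d²/268.2)]. At T2, 1/5 + 47.61/268.2 = 0.378.

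- ρ = 0.5: SE 0.0774, z = 0.175/0.0774 = 2.26, power 0.62.
- ρ = 0.7: SE 0.0841, z = 2.08, power 0.55.
- Direct T2 comparison: SE = √(2/230) = 0.0933, z = 3.22, power 0.90.

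The slope has SE √[(2/230)(1 − ρ)/268.2], which is 0.0040 at ρ = 0.5 and 0.0031 at ρ = 0.7. Under the held effect the slope test rejects with probability 0.65 to 0.85 (z = 2.33 to 3.01), suggesting a growing effect although nothing changes after T2. Under the fade it detects the decline with probability only 0.13 to 0.19 (z = 0.83 to 1.08 in size).

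**Step 3: time coding.** Coding visits as waves 0 to 4, the held effect reads 0.12/0.18/0.24/0.30/0.36, so T2 is 40% too small and the 12-month value is exact.

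**Step 4: line fitted to T2–T5 only.** Deviations −9, −3, 3, 9; sum of squares 180.

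- Held 0.30: slope 0, every visit exact. T2 power, using 1/4 + 81/180 = 0.70 in the variance, is 0.92 to 0.94.
- Fade 0.40/0.30/0.20/0.10: linear across these visits, every visit exact.
- Faster fade 0.40/0.20/0.10/0.05: slope = −3.45/180 = −0.0192; the line reads 0.360/0.245/0.130/0.015, so the largest error is 0.045.

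The size of the problem therefore turns on whether T1 is a modelled outcome.

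**The case against.** The strongest reply is that the protocol does not commit to the model that produces the large errors. The word linear does not appear, no time coding is given, and slope and re-centering are also used with piecewise or polynomial growth models. The account is introduced as an example in a condensed article. Nor does the text say that T1 is an outcome: Aim 1 lists the post-intervention and follow-up visits, and the example runs "by systematically re-centering the intercept (e.g., model 1: intercept at post treatment, model 2: intercept at 6 months, etc", with no baseline intercept. Fitted to T2–T5, the line loses nothing in either main scenario. The protocol also predicts no trajectory for ARCS and does not rank T2 above the other visits.

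Much of this stands. A reader might infer that the plan certainly biases the effect at every visit; the document does not support that. Linear time and T1 as an outcome are both inferences, and even when both hold the 12-month error is only 0.01 to 0.02 in months coding.

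Two things remain. A single slope with a single time-by-arm term is what the text describes, so its claim to give the effect at each time point depends on a shape restriction that it does not acknowledge. And a change outcome, ARCS measured at T1 to T5, and a covariate list without baseline ARCS make T1 in the outcome vector the more natural reading.

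**Conclusion.** The concern holds in conditional form. As written, the method evaluates one fitted line at several times and does not estimate separate visit effects.

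If time is linear and T1 is a modelled outcome, a held effect of 0.30 is understated by about 0.12 SD at T2 and overstated by about 0.04 at 18 months, with T2 power of 0.55 to 0.62 in place of 0.90 at N = 460. A steady fade is largely hidden. If only T2–T5 enter the model, the bias is zero for a held or linearly fading effect and at most 0.045 for the faster fade checked.

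The figures rest on assumed visit times, correlation, covariance, effect shapes and complete follow-up. They should not be read as the bias this trial will have. The sample of 368 in Sample size {14} belongs to the mediation analysis, so the power figures here use the target of 460.

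**What to change.** Replace the re-centered models with one mixed model for repeated measures:

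- visit (T2–T5) as a categorical factor, with arm-by-visit terms;
- unstructured within-person covariance;
- baseline ARCS as a covariate, or T1 kept in the outcome vector with arm means constrained equal at baseline. Say which, because the size of the bias turns on it;
- the arm contrast at each visit taken directly from this model.

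If a trajectory is wanted, report a piecewise slope with a knot at T2 as a secondary analysis. In a simulated check with a true effect of 0.35 held from T2 on, that form returned 0.346, 0.349, 0.353 and 0.356 at T2–T5, where the single line returned 0.193, 0.266, 0.338 and 0.410.

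The cost is a change of wording and a few extra parameters, negligible at N = 460. It uses the same data. Recruitment is expected to run to April 2027 and no interim analysis is planned, so the change can still be pre-specified.
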